The main goal of this study is to verify the efficacy of psychological treatment, in the young population, when this treatment includes biofeedback of changes in some physiological features (such as SCL, HR and HRV) associated with the imminent onset of an aggressive outburst. Apart from the main goal, other aspects will also be explored: how aggressive episodes influence physiological signals (HR, HRV, SCL in particular) identifying the most significant features; and how different scenarios (home, lab) influence this variability in physiological signals.

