Fig 2 depicts the phases and actions in this important session. The experimenter will tag the beginning of each phase in this session and will mark the moment when the impulsive outburst appears. By doing so, researchers will be able to analyze offline how the physiological information changed and how it can be included in the therapy. There will be a digital diary to collect tests outcomes and any relevant information regarding the patient during the session, including whether the outburst was evoked successfully. Data will be discarded from analysis when it is not possible to evoke the outburst.

The data collected in this block will allow assessing the influence of an aggressive episode on physiological signals. This will be used to teach individuals to identify when an outburst is about to occur, and prevent it.

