### Metrics

As a general procedure, outliers will be identified by applying the interquartile range method. We will then examine each outlier assess whether it could be attributed to measurements errors, technical issues, or specific characteristics of the participant. Data points will be excluded only when a clear justification exist (e.g: confirmed recording errors).

Continuous variables will be summarized using the mean and standard deviation (SD) when data are normally distributed. For variables that do not meet the normality assumption, we will report the median and interquartile range (IQR). Normality will be assessed through the Shapiro–Wilk test. Appropriate statistical tests (parametric or non-parametric) will be selected accordingly to the distribution of residuals.

**Psychological assessment.** Scores will be obtained by CACIA, STROOP, WCST, CBCL, and YSR tests at the beginning and at the end of the experiment. These tests contain 40 variables that will help assess the effect of the therapy and look into the underlying cognitive mechanisms regarding aggression, such as executive functions and other emotional or behavioral issues associated with it.

At the end of this section reader will find a list of the primary variables that directly measure the impact of the therapy and reflect key aspects related to self-regulation/-control, which are important to mitigate outbursts.

**Cardiac features.** One important feature, from which others can be derived, is instantaneous heart rate (HR). Both Empatica and Emotibit obtain HR from PPG signals by determining the position of their maximums and then calculating the time difference between two consecutive maximums.

Derived from HR, heart rate variability (HRV) in time analysis can be extracted from 2-minute windows by obtaining the root medium square (RMSSD) between maximums of the PPG peaks. The length of the windows will be selected to fulfill the requirements of frequency band analysis of the heart rate variability (HRV) spectrum [50].

HRV is especially interesting as it allows assessing the activity of the parasympathetic and sympathetic pathways of the autonomic nervous system (ANS) [51]. For instance, the ratio between low frequency, [0.04–0.15] Hz (LF) and high frequency, [0.15–0.4] Hz (HF), which is called the ratio between LF and HF (LF/HF), shows the balance between the SNS and the PNS.

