#### Assessment of cognitive therapy with biofeedback.

The main goal of this study is to verify the efficacy of the proposed therapy. At the beginning adolescents will fill in the CACIA, Stroop, WCST and CBCL tests. At the end of the therapy, these metrics will be assessed once more to compute the difference with the initial tests. These differences will be compared between the intervention and control groups to ascertain statistical significance. To this end, we will use the Mann-Whitney-Wilcoxon test, or the one-way ANOVA, depending on the distribution of residuals, to determine whether samples originate from the same distribution

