#### Significant physiological features for aggressive outbursts detection.

We will also extend the statistical analysis to gauge how an aggressive outburst influences all physiological signals. To attain this objective, we will collect features from the last minute of relaxation period, in order to build a set to compare with the features associated with the 60-second data segment that contains the aggressive episode. For each participant there will be a maximum of 7 sets of features for any physiological signal, which will be obtained from sessions S2–S4 and S6–S9, considering that the evoking phase is successful. Statistical analysis will be applied to every feature individually. Friedmann’s test or ANOVA, with repeated measures will be applied to assess the difference between measures before and during the outburst. Friedmann’s test is a non-parametric method suitable for analyzing ordinal data or data that do not meet the assumptions of normality and homoscedasticity; it is also specifically designed for repeated measures or matched group data, allowing for comparisons across multiple conditions or time points for the same subjects. ANOVA will be applied for normally distributed data.

The analysis will be applied to each participant individually and for all participants globally. In order to reduce biases among individuals, features obtained during the baseline phase will be removed from the other phases.

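### The outburst-physiology analysis mixes pre-therapy and therapy-block sessions across arms with no block or arm term, and HR, RMSSD and SCL, listed as primary, have no stated between-arm analysis

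*Protocol article*

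**What the plan says.** In the protocol article, the Analysis subsection on significant physiological features compares the last minute of relaxation with the 60-second segment containing the outburst. It caps the number of feature sets at seven per participant and signal, and draws them from both laboratory blocks: "which will be obtained from sessions S2–S4 and S6–S9, considering that the evoking phase is successful". Friedman's test or repeated-measures ANOVA is used "to assess the difference between measures before and during the outburst", and "The analysis will be applied to each participant individually and for all participants globally". Neither arm nor treatment phase is named as a factor.

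The Block 2 section says of S2–S4: "The data collected in this block will allow assessing the influence of an aggressive episode on physiological signals". The Block 3 section gives S5 to the intervention arm only, follows the evocation with therapy in both arms in S6–S9, and expects biofeedback participants to manage or avoid outbursts better.

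The Metrics section announces "a list of the primary variables that directly measure the impact of the therapy". The list itself, under Summary of primary variables, has a psychometric part and a physiological part; the latter names HR, HRV (RMSSD) and SCL. The efficacy analysis takes pre-to-post differences in test scores and says: "These differences will be compared between the intervention and control groups to ascertain statistical significance".

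**The concern.** S2–S4 precede S5 and all therapy. Most of S6–S9 does not. If the trial's own hypothesis is right, the arousal response in the two blocks differs, and it differs by arm. One global before-versus-during estimate then describes neither an untreated nor a treated outburst, but a mixture whose weights depend on arm and on which evocations succeeded. A reader of the results could not tell which features react to an outburst before treatment and which still react after it.

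The second problem is a mismatch inside the article. Three variables carry the primary label and are introduced as measures of therapy impact, but the three stated analyses compare test-score changes between arms, before with during, and home with clinic. The trial will hold pre-therapy and therapy-block physiology for both randomised arms, with no stated analysis that uses it to compare them.

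**Working it through.** **1. The plan's own figure.** S2–S4 gives 3 sessions and S6–S9 gives 4, so 3 + 4 = 7 sets. The stated maximum is reproduced.

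**2. Share of sets after exposure to S5 or therapy.** Inputs: 70 participants in equal arms (35 each), and every evocation assumed successful. Within S6–S9, therapy comes after the evocation, so the control arm's S6 set precedes any therapy.

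- Intervention arm: S6–S9 all follow S5, so 4/7.
- Control arm: S7–S9 follow a therapy session, so 3/7.
- Overall: (35 × 4 + 35 × 3) / (70 × 7) = 245/490 = 50%.

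**3. Baseline removal does not help.** The plan subtracts baseline features from the other phases. With D the outburst value, R the relaxation value and B the baseline of the same session, (D − B) − (R − B) = D − R. The baseline cancels, and a treatment-related change in D − R remains.

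**4. What mixing does to the mean.** If exposure shrinks D − R by a fraction f, the pooled difference is 1 − f × s of the untreated one, where s is the exposed share. The documents give no value for f; 20% and 50% are assumptions.

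| Scenario | s | f = 20% | f = 50% |
|---|---|---|---|
| Both arms respond | 245/490 = 0.50 | 0.90 | 0.75 |
| Only the intervention arm responds | 140/490 = 0.29 | 0.94 | 0.86 |

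**5. What dropping S6–S9 would cost.** With within-person correlation ρ between sets and equal variances, the standard error of a mean of n sets is proportional to √[(1 + (n − 1)ρ)/n]. The ratio for 3 sets against 7 is:

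- ρ = 0: √(7/3) = 1.53.
- ρ = 0.5: √[(2/3)/(4/7)] = √1.167 = 1.08.

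Signal-to-noise of the pooled analysis relative to S2–S4 alone, when both arms respond (the factors from step 4 times these ratios):

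| | f = 20% | f = 50% |
|---|---|---|
| ρ = 0 | 1.37 | 1.15 |
| ρ = 0.5 | 0.97 | 0.81 |

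Above 1, pooling detects more; below 1, it detects less. The direction depends on ρ and f, and the documents give neither.

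**6. Per-participant tests.** For Friedman's test with two conditions and all n sets agreeing, the statistic equals n. With n = 3 it is 3 on 1 degree of freedom, p = 0.083, so three sets can never reach 0.05 on this test.

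**7. Primary variables against analyses.**

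| Stated analysis | Variables | Contrast |
|---|---|---|
| Assessment of cognitive therapy with biofeedback | Psychological test scores | Between arms |
| Significant physiological features | Physiological | Before vs during outburst |
| Lab and home scenarios | Physiological | Home vs clinic |

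No row compares HR, RMSSD or SCL between arms. The missing-data section refers to two compared groups and covers physiological variables, but names no test.

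**The case against.** Several points on the other side stand.

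- **Block 2.** A reader might infer that the article reserves this question for Block 2 and then contradicts itself. It does not: the Block 2 section says those data allow the assessment, not that only they do, and goes on to describe their use in teaching participants to recognise an outburst.
- **The aim.** A reader might also infer that the target is the untreated outburst. The Introduction asks how aggressive episodes influence the signals, without that limit, and places the question apart from the main goal. The Conclusion foresees a warning signal for people who apply learned skills, so features that still react after training matter too. It therefore cannot be said that pooling discards the features a warning device needs.
- **Precision.** Falling from 7 sets to 3 is a real loss, and with weakly correlated sets the pooled analysis detects more. This argues against making S2–S4 the only analysis set.
- **Selection.** Sessions without an evoked outburst are discarded. If therapy prevents outbursts, fewer exposed sets remain and the 50% share falls. Any between-arm contrast in S6–S9 would then compare sessions selected after randomisation, possibly differently by arm. The VR platform section also shows biofeedback values in the relaxation scenes; if they are displayed to the intervention arm in S6–S9, the relaxation reference differs by arm. The text does not settle this.

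Two points stand only in part. The sentence on primary variables sits under Psychological assessment, so it could be read as covering the tests alone; but the list it points to has an explicit physiological part. An analysis plan could add arm or phase terms; but the article already fixes the sessions, the contrast, the tests and the pooling, and Friedman's test leaves no room for such terms. The mismatch between the primary list and the analyses is within the article.

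**Conclusion.** The point holds in a limited form. The global before-versus-during estimate mixes untreated and possibly treated responses, with up to 4/7 exposed sets in the intervention arm and 3/7 in the control arm if every evocation succeeds. The analysis is mixed, not invalid, and the objective it serves is secondary to efficacy. A reader might infer a 10–25% understatement from step 4, but that rests on an assumed reduction of 20–50% in both arms; it is 6–14% if only the intervention arm responds, and no figure can be taken from the documents. Whether pooling gains or loses power is likewise open.

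The second part rests on text alone: HR, RMSSD and SCL are listed as primary variables, and no stated analysis compares them between arms. Given the selection on evoked outbursts, such a comparison would be exploratory and could not be read as a clean treatment effect. Both parts merit correction because the change is small and alters what the trial can conclude.

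**What to change.** In the subsection on significant physiological features:

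- Keep all seven sets for the global analysis. Add block (S2–S4 vs S6–S9) and arm, with their interactions with before/during. If Friedman's test is used, report the result by block and arm instead.
- Report the S2–S4 estimate as the treatment-free result.
- Keep the per-participant tests on all available sets, and label them descriptive.

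For HR, RMSSD and SCL, do one of two things: add an exploratory between-arm comparison of each participant's mean during-minus-relaxation response in S6–S9 minus that in S2–S4, or stop labelling these variables as primary measures of therapy impact. If the comparison is added, state that it is conditional on an evoked outburst, report the number of successful evocations by arm and block, and note that the relaxation reference may differ by arm if biofeedback is displayed in the VR relaxation phase.

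The cost is a few lines of analysis text and slightly more analysis, with no new data. Block-specific estimates, from at most 3 or 4 sets per participant, will be less precise than the pooled one.

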## Materials and methods

### Participants

As explained above, the early onset of aggressive behavior is linked to higher biological risks and often leads to persistent antisocial behavior, highlighting the importance of applying treatment at early age. For this reason, the group to be studied will consist of 70 participants aged 10–16 years. They will be recruited from the INEBIR clinic, where the experimental sessions will be carried out, and other participants will be recruited from the Instituto Hispalense de Pediatría. The sample size was by analyzing the differences of the means according to a Student’s t with a confidence level of α=0.05, a test power of 1−β = 0.8 and a moderate effect size [30]. A moderate effect size (Cohen’s d = 0.5) represents a practically meaningful difference in the context of clinical decision-making, even if smaller effects may also be statistically detectable in larger samples and it is a commonly used convention in behavioral and clinical research when planning exploratory studies [31]. A moderate effect size results in 62 participants. For a small effect size (Cohen’s d = 0.2), we would need to recruit more than 300 participants, and we do not have the human and material resources to complete this study in a relatively short time. Additionally, to account for potential non-response or dropout, we included an additional 10%, bringing the final target sample size to 70 participants. This approach ensures sufficient power to detect differences between groups while anticipating common challenges in recruitment and retention.

To participate in this study, the following inclusion criteria will be applied:

Adolescents aged 10 to 16 whose parents seek professional help because their son or daughter exhibits aggressive outbursts that they are unable to manage.Intermittent aggressive episodes with a frequency of at least once a week in the two months prior to the start of the intervention.Not presenting some of the following:History of bipolar or psychotic disorder.Head trauma with loss of consciousness for more than 60 minutes.

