HR and HRV will be used for biofeedback, although a much richer feature set will also be included for offline analysis [52].

**Skin conductance level (SCL) measurements.** The variation of the electrical conductance is referred to as EDA which is primarily due to sweat gland secretion. This activity is closely linked to the sympathetic nervous system, which is responsible for the body’s “fight or flight” response and therefore used as an indicator of physiological arousal, emotional responses, and stress. The two main components derived from EDA are skin conductance response (SCR) and skin conductance level (SCL).

SCL is the parameter that will be included in biofeedback and represents the baseline level of skin conductance over time, linked to emotional arousal.

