## Conclusion

By using biofeedback with cognitive, behavioral and emotional self-regulation therapies, we aim to improve the social skills of people with emotional dysregulation and reduce the frequency of aggressive episodes. This randomized control trial seeks to evaluate the effectiveness of including biofeedback in the therapy.

Although we will use HR, HRV and SCL for biofeedback purposes, a wider set of physiological features will also be studied. The goal is to pinpoint a small and significant set of features that are the best predictors for an incoming outburst.

This reduced set of features could allow designers to develop a minimal piece of equipment. The signals in the ensuing set could then be merged into a unique warning signal before the outburst so that people can apply the learned self-regulation mechanisms, and avoid or minimize the aggressive episodes.

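### Physiological features are to be chosen by significance from many separate tests, overall and within each participant, with no protection against chance findings; the within-participant tests are also unreliable at seven pairs or fewer

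*Protocol article*

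**What the plan says.** The Analysis subsection on significant physiological features compares each feature in the last minute of relaxation with the same feature in the 60-second segment containing the outburst. The test is Friedman's or a repeated-measures ANOVA, depending on the distribution. Three statements fix how often it is run:

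- "Statistical analysis will be applied to every feature individually"
- "The analysis will be applied to each participant individually and for all participants globally"
- "For each participant there will be a maximum of 7 sets of features for any physiological signal", the sessions being S2–S4 and S6–S9, provided that evoking the outburst succeeded.

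Metrics widens the list of features: "HR and HRV will be used for biofeedback, although a much richer feature set will also be included for offline analysis". The number of features is not given.

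The use of the results is stated in two places. The Introduction includes finding the most significant features among the aspects to be explored beside the main goal. The Conclusion says "The goal is to pinpoint a small and significant set of features that are the best predictors for an incoming outburst", and foresees minimal equipment and a single warning signal based on that set.

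The only significance level in the article is in the sample size paragraph under Participants ("with a confidence level of α=0.05"). It is not restated for the feature tests.

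**The concern.** Testing many features one at a time and keeping the significant ones is a selection procedure, even when the aim is called exploratory. As described, it has no error-rate control, no validation step and no rule for combining the overall and individual results. A feature unrelated to outbursts could enter the set by chance and be carried into the equipment that the Conclusion has in mind.

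The participant layer has a second problem, which lies in what is written and not in what is left out. A test on at most seven pairs has very few possible outcomes. Whether a participant can show a significant feature at all then depends partly on how many of that participant's sessions produced an outburst. A correction added in a separate analysis plan could repair the overall tests, but it would not make a rank test on three to five pairs informative.

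**Working it through.** **Inputs**

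- Level: 0.05, from the sample size paragraph; applying it two-sided to the feature tests is an assumption.
- Named signals: 3 (HR, RMSSD, SCL), from the summary of primary variables.
- Size of the wider feature set: not stated; 10 and 20 are assumed.
- Correlation between features: not stated; 0 to 0.8 is assumed.
- Conditions: 2 (relaxation, outburst).
- Pairs per participant: S2–S4 gives 3 and S6–S9 gives 4, and 3 + 4 = 7, which reproduces the article's maximum.

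**All-participant tests**

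If all m features are null and independent, the chance of at least one false positive is 1 − 0.95^m:

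- m = 3: 1 − 0.857 = 0.143
- m = 10: 1 − 0.599 = 0.401
- m = 20: 1 − 0.358 = 0.642

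Physiological features are correlated, which lowers these figures. Simulating equicorrelated normal test statistics (40,000 draws, rejection at |z| > 1.96) gives:

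| Features | r = 0 (formula) | r = 0.5 | r = 0.8 |
|---|---|---|---|
| 3 | 14% | 13% | 10% |
| 10 (assumed) | 40% | 28% | 17% |
| 20 (assumed) | 64% | 42% | 22% |

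**Within-participant tests, Friedman route**

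With two conditions and n pairs, let x be the number of pairs in which the outburst value is the higher. The rank sums are n + x and 2n − x, and Friedman's statistic becomes

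Q = (2/n)[(n + x)² + (2n − x)²] − 9n = (2x − n)²/n, on 1 degree of freedom.

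This is a sign test. Its largest value is Q = n, when all pairs agree in direction. The chi-square critical value is 3.84.

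- n = 3: the maximum Q is 3, below 3.84, so the test can never reject.
- n = 4 to 7: the maximum Q is 4, 5, 6 and 7, all above 3.84. With one pair discordant, Q is (n − 2)²/n = 1.0, 1.8, 2.67 and 3.57, all below 3.84.

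So with four to seven pairs, only complete agreement rejects. Under the null its probability is 2 × (1/2)^n, which is also the smallest exact two-sided p-value.

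| Pairs | Smallest chi-square p | True size using chi-square p | Smallest exact p | Can exact p reach 0.05? |
|---|---|---|---|---|
| 3 | 0.083 | 0 | 0.25 | no |
| 4 | 0.046 | 12.5% | 0.125 | no |
| 5 | 0.025 | 6.25% | 0.0625 | no |
| 6 | 0.014 | 3.1% | 0.031 | yes |
| 7 | 0.008 | 1.6% | 0.016 | yes |

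The same nominal 0.05 thus corresponds to a true size anywhere from 0 to 12.5%, depending on the number of usable sessions. The Block 2 description discards data when no outburst is evoked, and Study limitations says that inhibition in the laboratory may reduce the valid data. Fewer than seven pairs is therefore a case that the article itself foresees as possible.

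**The case against.** The strongest reply is that this is a condensed article with no analysis plan shown, that the aim is exploratory, and that a multiplicity rule for such an analysis commonly sits in the plan. For the all-participant layer this carries real weight and is the main reason the point is minor. It does not answer the participant layer, where the article itself fixes the test and the maximum number of pairs. Nor is the exploratory label carried through: HR, RMSSD and SCL are listed as primary variables, and the Conclusion draws design consequences from the selected set.

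A reader might go further than the documents allow in four ways.

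- *The selected set will contain chance findings.* This is not shown. The risk depends on how many features are tested, how many are truly null and how they correlate. HR, HRV and SCL are chosen because they are expected to respond to arousal, so the all-null case is a worst case.
- *Dozens of false positives will arise within participants.* With 70 participants and 3 signals there are 210 tests, and 210 × 0.125 is about 26. That figure needs every signal null in every participant, exactly four pairs each, chi-square p-values, the Friedman route throughout and no dropout. At six or seven pairs the test is conservative.
- *Individual results put features into the set.* The article does not say so. It gives no rule either way.
- *Many sessions will be lost.* Study limitations says only that the valid data might be reduced.

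The ANOVA alternative does not have the discreteness shown above and holds its nominal size where its normality assumption is met.

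**Conclusion.** The point holds as a minor one. Significance is the stated aim of feature selection, and the selection as described has no protection against chance findings. For the all-participant tests, the chance of at least one false feature is about 10–14% for the three named signals and 17–40% for an assumed ten. Those figures assume that all features are null, a two-sided 0.05 level and correlations from 0.8 down to 0.

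Within participants, the Friedman route is unreliable at these numbers whichever p-value is used, and its result depends in part on how many sessions are successfully evoked. The size inflation at four and five pairs rests on chi-square p-values being used. The inability to reject at three pairs does not.

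None of this touches the between-group comparison of psychometric change, which is the main goal. Nor does it decide which signals are fed back, since HR, HRV and SCL are already fixed for that purpose.

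**What to change.** 1. In the subsection on significant physiological features, state that features are selected only from the all-participant analysis, with Benjamini–Hochberg control at a 5% false discovery rate across all features tested there. With ten features, for example, the smallest p-value is compared with 0.05 × 1/10 = 0.005, the second with 0.05 × 2/10 = 0.010, and so on up to 0.05.
2. Report the within-participant results as effect estimates and counts of direction (for instance, how many of the usable sessions showed a rise), without significance claims.
3. In the Conclusion, call the selected set hypothesis-generating.

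The cost is a few sentences and one line of analysis code, with no new data. The downside is that fewer features may be declared significant and individual p-values are given up.

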### Study limitations

The application period of biofeedback therapy, along with the time required to recognize the physiological variables used to identify the preparatory state that precedes an aggressive outburst, might be too short to achieve significant results to validate the therapy. Should it be the case that the results do not show changes in the subjects, sessions S6–S9 will be repeated.

If an aggressive impulse involves numerous movements by the individual, the capture of physiological signals, and consequently the extraction of features derived from those signals, could be significantly disrupted, which in turn may affect the detection of the preparatory state.

There may also be an environmental inhibition effect when attempting to provoke an impulsive response in the laboratory. This could be a serious limitation, as it might significantly reduce the amount of valid data available for training artificial intelligence models, thereby diminishing the power of the proposed statistical analysis.

The equipment used to measure physiological signals could be damaged during aggressive responses. Although replacement materials have been planned, they might be insufficient, requiring additional budget and time to conduct the tests.

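### The one-feature-at-a-time tests described cannot by themselves show which features best predict an incoming outburst

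*Protocol article*

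**What the plan says.** The Introduction of the protocol article lists, as an aspect to be explored beside the main goal, how outbursts influence the signals, "identifying the most significant features". The Conclusion goes further: "The goal is to pinpoint a small and significant set of features that are the best predictors for an incoming outburst". It adds that the signals in the reduced set could later be "merged into a unique warning signal before the outburst".

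The analysis is given under *Significant physiological features for aggressive outbursts detection*. For the reference state, "we will collect features from the last minute of relaxation period"; these are compared with "the 60-second data segment that contains the aggressive episode". Friedman's test or repeated-measures ANOVA "will be applied to assess the difference between measures before and during the outburst", and "Statistical analysis will be applied to every feature individually". The comparison is made within each participant and over all participants, after removing baseline values.

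The Metrics section derives HRV from HR and says that a wider feature set than the one used for biofeedback will be analysed offline. Study limitations mentions "valid data available for training artificial intelligence models", but no such model is described in the Analysis section.

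**The concern.** The aim and the method answer different questions. A before/during test on one feature asks whether its typical value moves. A claim about best predictors needs three other things:

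- how well the feature, or the set, tells one state from the other in a child not used to choose it;
- whether each feature adds information once the others are known, which matters here because several cardiac features come from the same beat series;
- whether the change is present before the outburst, since a warning is meant to precede it.

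The analysis described yields none of these. Followed as written, it can list features that shift during an outburst. It cannot show that they are the best predictors or a sufficient minimal set. That matters because the Conclusion offers the reduced set as a basis for a small device that warns children.

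**Working it through.** **Inputs from the protocol article.** 70 participants (Participants); at most 7 feature sets per participant (the feature analysis); α = 0.05 (stated for the sample size, assumed here for the feature tests and taken as two-sided). **Assumed, not in the document:** correlation r between a child's relaxation and outburst values, 0 to 0.7; normally distributed values.

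**1. The plan's own figure.** Sessions S2–S4 give 3 sets and S6–S9 give 4; 3 + 4 = 7, as stated. The most pairs available is 70 × 7 = 490.

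**2. What a just-significant result guarantees.** With one pair per child, the smallest significant shift in SDs of the change is dz = t(0.975, n−1)/√n. For n = 70, dz = 1.995/8.367 = 0.238.

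- Share of children moving in the expected direction: Φ(0.238) = 0.594, or 59% (chance 50%).
- AUC for outburst against relaxation: Φ(dz·√(1−r)).

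| Pairs | dz | AUC, r = 0 | r = 0.5 | r = 0.7 |
|---|---|---|---|---|
| 70 | 0.238 | 0.594 | 0.567 | 0.552 |
| 490, treated as independent | 0.089 | 0.535 | 0.525 | 0.519 |

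More pairs make p < 0.05 a weaker guarantee of discrimination.

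**3. The Friedman route.** With two conditions and one pair per child, the statistic depends only on the number x of pairs going the same way: χ² = (2x−n)²/n, significant above 3.84. For n = 70, x = 44 gives 18²/70 = 4.63, while x = 43 gives 16²/70 = 3.66. So 44 of 70 (63%) suffices. Of 490 pairs treated as independent, 267 (54.5%) suffice: 44²/490 = 3.95.

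**4. The per-participant analysis.** With the maximum of 7 pairs, 7 of 7 gives χ² = 49/7 = 7 (p = 0.008); 6 of 7 gives 25/7 = 3.57 (p = 0.059). A single child's data pass only if every session agrees.

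**5. Redundancy.** Take five features, each shifted by d = 0.24 SD (single-feature AUC Φ(0.24/√2) = 0.567), with mutual correlation ρ. Their equal-weight sum has D = d·√(5/(1+4ρ)).

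- ρ = 0: D = 0.537, AUC = Φ(0.537/√2) = 0.648.
- ρ = 0.9: D = 0.250, AUC = Φ(0.250/√2) = 0.570.

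The single-feature results can be identical in both cases, so separate tests cannot tell whether one feature would do the work of five.

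**6. Timing.** The tested window contains the episode. Even a very strong result would show recognition of an outburst in progress, not warning of one to come.

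**7. The other end of the range.** Shifts of d = 1.5 and d = 2 would give AUCs of 0.86 and 0.92 (Φ(d/√2)). The document gives no expected effect for these features, so nothing in it says which end applies.

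**The case against.** The stated objective of this analysis is to gauge how an outburst influences the signals, and before/during tests answer that. The aim is exploratory. The predictor claim stands in the Conclusion, followed by conditional remarks about future use. Study limitations shows that predictive modelling is contemplated, and an article may leave model details to a fuller plan. The contrast is relaxation against a provoked outburst, so effects may be large. The per-participant analyses would help expose a shift that is inconsistent across children.

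Much of this stands. A reader might infer that the predictors will be picked or ranked by p-value, so that the chosen set will be near chance. The document does not support that: no sentence states a selection rule or a ranking, and the low AUCs describe only a feature at the edge of significance under an assumed correlation. Nor is the absence of modelling detail a fault in an article.

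What does not fall away is the mismatch. The section does fix a single-feature method, the aims speak of significance, and the mention of models is not tied to choosing features. The per-participant tests, with at most 7 pairs, are weak and do not measure accuracy in new children.

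**Conclusion.** The point holds in a limited form. The tests described can show that features change during an outburst; they cannot by themselves support the statement that a small set of them best predicts an incoming one, because they measure neither discrimination, nor redundancy, nor lead time.

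The AUC of 0.55 to 0.59 is a floor, not a forecast: it assumes one pair from each of 70 children, a result exactly at p = 0.05, normal values and r between 0.7 and 0. Accuracy may be much better, but the planned output would not reveal it.

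The efficacy comparison does not depend on this analysis. The signals shown in therapy (HR, HRV and SCL) are fixed in advance and are not chosen by it.

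**What to change.** Keep the Friedman and ANOVA tests as a description of how outbursts affect the signals. For the predictor aim, add:

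- **Event window:** the already recorded segment before the onset that the experimenter marks, with its length fixed in advance, against the relaxation segment.
- **Model:** one joint model of the baseline-corrected features, for example penalised logistic regression. Other joint methods would also serve.
- **Validation:** leave out whole participants, with feature selection repeated inside each fold.
- **Report:** out-of-sample AUC, sensitivity and false-alarm rate, with intervals clustered by child. State that false alarms are measured against laboratory relaxation.

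If this is not wanted, reword the Conclusion to claim only features that change during an outburst.

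The cost is some extra analysis and no new data collection. Sessions in which onset comes too soon for a full pre-onset window would drop out of this part, and the resulting accuracy may look less favourable than a list of significant features.
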